### Publications

The final study results will be submitted as a manuscript for publication. No restrictions on publication exist. This information will be made available to the recruitment clinics and study participants.

## Discussion

The results of the current study will shed light on whether targeted cognitive training programs can improve not only cognition, but also daily functioning in the lives of schizophrenia patients. Given the recently widespread availability of “brain training” games on the Internet, the benefits of cognitive training for individuals with schizophrenia should be examined to identify whether these games can be recommended as part of an intervention program. Overall, the current study may benefit individuals with schizophrenia who want to enhance their cognition.

The strengths of the current study include that two more specific training program are being utilized, which will provide more specific information on the mechanisms of training-related gains than the broad-based training programs that have been used in the previous literature. Additionally, the current study is employing multiple measures to assess each cognitive domain and thus will provide a more comprehensive analysis of training gains. Both a strength and limitation of the current study is the number of outcome measures that are being utilized. This is a strength of the design, given that it allows us to thoroughly examine many different near- and far-transfer effects associated with working memory and processing speed training in schizophrenia. However, this may also be viewed as a limitation of the current design, as it may lead to errors associated with multiple comparisons. To address this issue, composite measures will be used in the statistical analyses where applicable (for example, a working memory composite). In addition, two primary outcome measures have been chosen for each group, as described above (that is, working memory composite and fluid intelligence composite for the working memory group, and processing speed composite and fluid intelligence composite for the processing speed group). Finally, a limitation with this line of research is the difficulty in obtaining pure measures and pure training programs of each cognitive domain. To address this issue, we have included multiple assessment measures of each cognitive domain. With regards to the training programs, we recognize the difficulty in creating games that solely train working memory abilities and processing speed abilities, though we are confident that the selected games predominantly train the cognitive domain of interest. However, we will also examine potential gains in other domains, as described above.

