### Objectives and hypotheses

This study will investigate 1) near-transfer gains associated with working memory and processing speed training in schizophrenia patients (that is, gains in the working memory or processing speed domains, respectively); 2) far-transfer gains associated with working memory and processing speed training in schizophrenia patients (that is, gains in other neurocognitive domains, primarily fluid intelligence, and gains in social cognition); and 3) real-world gains associated with working memory and processing speed training in schizophrenia patients (that is, gains in daily functioning). In addition, exploratory analyses will examine the effect of individual difference variables (that is, sleep quality and intrinsic motivation) on training-related gains. The primary outcome measures are as follows: working memory, processing speed, and fluid intelligence.

The corresponding hypotheses are as follows: 1) post-training performance in working memory and processing speed will improve in the working memory training group and processing speed training group, respectively, relative to the no-training control group (that is, both training groups will show near transfer in their own domain); 2) both working memory and processing speed training will lead to more generalized improvements in other neurocognitive domains, particularly fluid intelligence, compared to the no-training control group, as well as enhancements in social cognition relative to the no-training control group; and 3) both working memory and processing speed training will lead to more improvements in daily functioning compared to the no-training control group. Given the current paucity of research comparing the gains associated with specific training programs, no hypotheses are made with regards to which training group (that is, working memory or processing speed) will show greater improvements in neurocognition, social cognition, or daily functioning. Rather, comparisons between training groups will be exploratory in nature.

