### Recruitment process and study population

Up to 81 schizophrenia patients will be recruited. This is based on a power calculation with an alpha-level of .05, power of .80, and an effect size of *d* = .70, with the effect size derived from a recent study examining a more specific cognitive remediation program (that is, auditory working memory training) in schizophrenia [58]. Importantly, this sample size accounts for dropout rates of up to 10 %, based on previous cognitive training studies [82]. Recruitment status is currently pending, with plans to start in January 2016. Patients will be recruited through outpatient clinics at Foothills Medical Centre and through community support programs in Calgary, Alberta, after receiving appropriate permissions to enter the clinics and discuss the study. Participants will also be recruited through an existing participant database at the University of Calgary. Inclusion criteria for all participants will be as follows: (1) a diagnosis of schizophrenia or schizoaffective disorder, assessed with the Structured Clinical Interview for DSM-5 (SCID-5) interview; (2) age 18 to 65 years; (3) no uncorrected visual impairment, including color blindness, determined by self-report; (4) no uncorrected hearing impairment, determined by self-report; and (5) able to provide informed consent, determined by the clinical experience of the researchers. Exclusion criteria will be as follows: (1) meeting Diagnostic and Statistical Manual - 5^th^ edition (DSM-5) diagnostic criteria for a current major depressive episode, manic episode, or hypomanic episode, assessed with the SCID-5 interview; (2) use of electroconvulsive therapy (ECT) or transcranial magnetic stimulation therapy (TMS) within the past month, determined by self-report; (3) recent (that is, within past 3 months) history of substance-use disorder (excluding nicotine, cannabis, or caffeine), assessed with the SCID-5 interview; (4) diagnosed with a medical condition known to affect cognition (for example, endocrine disease or uncontrolled diabetes), determined by self-report; and (5) score less than 70 on the Wechsler Abbreviated Scale of Intelligence (WASI-II). In addition, only individuals who have access to the internet on a home computer will be eligible to participate in the study.

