### Statistical analysis

The following demographic variables at screening will be summarized: ethnicity, sex, age, and education. Between-group analyses of variance (ANOVAs) and chi square analyses will be used to examine any baseline differences between groups in demographics, individual characteristics (for example, sleep), cognition, and/or functioning. Any baseline differences will be corrected in all further analyses as appropriate.

Next, a three-group (working memory training, processing speed training, or no training) x time (pre-training or post-training) repeated measures ANOVA will be conducted to test for significant group differences in each domain of neurocognition (that is, memory, processing speed, executive functioning, and fluid intelligence) over time. Follow-up one-way repeated measures ANOVAs will be conducted as necessary to further examine the main effects of time. Follow-up independent *t*-tests will be conducted to examine differences in training- related gains between each training group and the no-training control group, based on the above-described *a priori* study objectives. Cohen’s *d* effect sizes will be reported. Notably, composite measures will be used where applicable (for example, a working memory composite, a processing speed composite).

Similarly, a group x time repeated measures ANOVA will be conducted to test for significant group differences in each social cognition task and each measure of daily functioning, with follow-up one-way repeated measures ANOVAs to follow-up on main effects of time and independent *t*-tests to examine group differences. Again, Cohen’s *d* effect sizes will be reported.

Finally, exploratory simple regression analyses will be conducted to examine potential moderating factors of training-related change. For any aspects of cognition and functioning that show significant training-related gains, regression analyses will be conducted using individual difference variables (for example, medication usage, sleep quality, duration of illness, intrinsic motivation) as the independent variable and change scores for each cognitive or functional domain as the dependent variable.

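### The primary set is stated inconsistently, and the stated answer to multiple comparisons leaves four training-versus-control tests with no error control

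*Protocol article*

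**What the plan says.** The Abstract and Objectives and hypotheses give one trial-wide list: "The primary outcome measures are as follows: working memory, processing speed, and fluid intelligence".

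Table 1 has a single primary-or-secondary column. It marks seven tasks Primary: three for working memory, two for processing speed, two for fluid intelligence. Each also carries a near- or far-transfer hypothesis for both training arms.

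The Discussion says of the number of outcome measures that "this may also be viewed as a limitation of the current design, as it may lead to errors associated with multiple comparisons". It answers with composites and with a narrower set: "two primary outcome measures have been chosen for each group, as described above". These are the working memory and fluid intelligence composites for the working memory arm, and the processing speed and fluid intelligence composites for the processing speed arm.

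Statistical analysis plans a group-by-time ANOVA for each neurocognitive domain, then follow-up t-tests of gains in each training arm against control. It adds that "composite measures will be used where applicable". It states no significance level. The only one in the article is in the sample-size sentence: "alpha-level of .05, power of .80", with "an effect size of *d* = .70".

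**The concern.** Two problems compound each other.

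First, the primary family is not fixed. The objectives' list applied to both arms gives six training-versus-control contrasts; the Discussion gives four. Processing speed in the working memory arm shows the conflict: Table 1 makes it a primary far-transfer outcome, while the Discussion does not make it primary. The Discussion points back to an earlier description of the per-arm choice, but none exists.

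Second, the remedy does not do what it is offered for. Composites and a per-arm choice reduce the number of tests. They do not limit the error across those that remain.

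The Discussion wants the results to show whether such games can be recommended to patients. A false positive on a primary contrast, or a primary family settled after the data are seen, would weaken that use.

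**Working it through.** **Plan's own figure.** The article states no familywise error rate, so there is none to reproduce.

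**Inputs.**
- 81 patients allocated 1:1:1, so 27 per arm (Recruitment process and study population; Study design).
- Two training arms and one shared control. Training-versus-training comparisons are exploratory and not counted.
- Test level .05, taken from the sample-size sentence and assumed two-sided, because neither the test level nor the sidedness is stated.
- Correlation between domain gain scores: not given, so assumed from 0 to .9.

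**Step 1: count.** Discussion set: 2 arms x 2 composites = 4. Trial-wide list for both arms: 2 x 3 = 6.

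**Step 2: bound under independence.** 1 − (1 − .05)^4 = .185 for four tests. Within one arm, 1 − .95^2 = .0975.

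**Step 3: allow for the shared control and correlated outcomes.** Simulation of 100,000 trials with no true effect, 27 per arm, t-tests on gains at .05. Chance of at least one false positive:

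| Correlation | Four contrasts | Four, strictly gated by the domain's omnibus F | Six contrasts |
|---|---|---|---|
| 0 | .179 | .087 | .248 |
| .3 | .173 | .086 | .236 |
| .5 | .164 | .081 | .219 |
| .7 | .151 | .074 | .193 |
| .9 | .127 | .062 | .149 |

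**Step 4: how far a gate would help.** The gated column holds only when nothing is real. A true effect of one arm in a domain opens that domain's gate for the other arm. With independent domains and one null contrast left behind an open gate in each, the error is 1 − .95^3 = .143.

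**Step 5: check the proposed procedure.** Within an arm, fluid intelligence is tested only after near transfer succeeds, both at .025. If near transfer is null, an error requires rejecting it (at most .025). If it is real, the only possible error is on fluid intelligence (at most .025). Two arms: .025 + .025 = .05 at most, whatever the correlation and whichever effects are real.

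Raising the other arm's near-transfer test to .05 while also handing the same alpha to fluid intelligence would spend it twice. With one near-transfer effect certain and the rest null, the error is roughly 1 − .95 x .975 = .074 with fluid intelligence at .025, or 1 − .95^2 = .0975 at .05. Simulation gives about .073 and .096.

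**Step 6: power cost.** Two-sided two-sample t-test on gains, d = .70 on the gain scale:

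| Per arm | Alpha .05 | Alpha .025 |
|---|---|---|
| 27 | .71 | .61 |
| 24 (81 less 10% dropout is about 24.3 per arm) | .66 | .55 |

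**The case against.** The strongest reply is that the three statements largely nest. Seven tasks measure three domains, and the Discussion's four contrasts follow hypotheses 1 and 2: each arm on its own domain, and both on fluid intelligence. That is right. A reader might infer three incompatible definitions, but the documents do not support so strong a word. What stands is that Table 1 labels tasks Primary without an arm and that the per-arm assignment has no antecedent.

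A reader might also count seven tasks in two arms as fourteen primary tests and quote 1 − .95^14 = .51. The text does not support this. Neurocognition is to be analysed by domain, the Discussion names all three composites, and tasks within a domain are not independent.

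A third inference is that any one significant contrast makes the trial positive. No section defines success that way; the hypotheses are separate.

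On the analysis, the t-tests are called follow-up, so an omnibus gate is a natural reading and roughly halves the error under the complete null. But they are tied to the prior objectives and not to a significant interaction, and even a strict gate leaves more than 5%.

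Two further points have force. An analysis plan not shown here may set an adjustment, so its absence alone would be no finding; the criticism is of the remedy that the Discussion itself presents. And whether two different interventions sharing a control need one trial-wide rate is debated. Even per arm, two unadjusted tests reach up to .0975.

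**Conclusion.** The point holds in this limited form: the primary set is inconsistent and not fixed, and the stated remedy leaves four contrasts without stated error control. The chance of at least one false primary result under the complete null is about .16 to .18 for outcome correlations of 0 to .5 (.127 at .9), or about .08 to .09 (.062 at .9) under a strict omnibus gate.

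These figures assume that each contrast is tested at two-sided .05, with 27 per arm and equal variances; the gain-score correlations are assumptions. The conclusion that the error exceeds 5% holds under both the gated and ungated readings and at every correlation tried.

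**What to change.** 1. Use the Discussion's set in the Abstract, Objectives, Table 1 and Statistical analysis: working memory and fluid intelligence composites for the working memory arm, processing speed and fluid intelligence composites for the processing speed arm, each against control.
2. Relabel the seven tasks in Table 1 as components of composites. Make cross-domain contrasts secondary. Drop the where-applicable qualifier for the three primary composites.
3. Give each arm two-sided .025. Test its near-transfer composite first and its fluid intelligence composite only if the first succeeds, also at .025. Do not pass the same alpha to the other arm's near-transfer test as well.

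The text changes are small, and Trial status says recruitment has not begun. The real cost is power: about .71 to .61 per near-transfer contrast with 27 per arm, .66 to .55 with 24, at d = .70 on the gain scale. An arm without near transfer also cannot claim fluid intelligence.

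If the sponsor prefers control per arm, the same ordering at .05 within each arm costs no near-transfer power. The protocol should then say that error is controlled per arm and not across the trial, where it could reach .05 + .05 = .10.

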### Trial status

The current trial has received ethics approval from the University of Calgary Conjoint Health Research Ethics Board (CHREB). Recruitment of study participants has not yet commenced but is tentatively scheduled to begin in January 2016.

## Abbreviations

ANOVA: analysis of variance
CCFT: Cattell’s Culture Fair Test
CFQ: Cognitive Failures Questionnaire
CHREB: Conjoint Health Research Ethics Board
CWIT: Color-word Interference Test
D-KEFS: Delis-Kaplan Executive Function System
DSM-5: Diagnostic and Statistical Manual - 5^th^ edition
ECT: electroconvulsive therapy
EF: executive function
PANSS: Positive and Negative Syndrome Scale
RCT: randomized controlled trial
SCID-5: structured clinical interview for the DSM-5
SOFAS: Social and Occupational Functioning Assessment Scale
TMS: transcranial magnetic stimulation
UPSA: UCSD Performance-based Skills Assessment
WAIS-IV: Wechsler Adult Intelligence Scale – 4^th^ Edition
WASI-II: Wechsler Abbreviated Scale of Intelligence – 2^nd^ Edition
